## Abstract

**Background:**

Aneurysmal subarachnoid hemorrhage (aSAH) is a life-threatening neurosurgical emergency with a high mortality rate. Delayed cerebral ischemia (DCI) and cerebral vasospasm (CVS) are delayed products of early brain injury (EBI), which may constitute the principal determinant of an unfavorable patient prognosis. Consequently, the mitigation of DCI and CVS assumes paramount significance in the pursuit of enhanced patient outcomes. However, except for oral nimodipine, there is no effective therapy available in the current guideline. Hence, the exigency arises to proffer novel treatment paradigms. The diversity of hydrogen therapeutic targets has been largely reported in basic research, unveiling its latent capacity to ameliorate EBI in aSAH patients.

**Methods:**

Early *H*ydrogen–*O*xygen Gas *M*ixture *I*nhalation in Patients with Aneurysmal Subarachnoid Hemorrhage (HOMA), a single-center, prospective, open-labeled, randomized controlled clinical trial, endeavors to evaluate the efficacy and safety of hydrogen–oxygen gas mixture inhalation therapy in aSAH patients. A cohort of 206 patients will be randomized to either hydrogen–oxygen gas mixture inhalation group (8 h per day, 3 L/min, hydrogen concentration of 67%, oxygen concentration of 33%) or oxygen inhalation group (8 h per day, 3 L/min, oxygen concentration of 33%) within 72 h after aSAH and treated for 7 days in the ICU ward. The primary outcomes are the incidence of DCI and CVS during hospitalization.

**Discussion:**

The HOMA aims to evaluate the effectiveness of hydrogen–oxygen gas mixture inhalation therapy in preventing DCI or CVS and improving outcomes in aSAH patients. Notably, this is the first large-scale trial of hydrogen therapy in aSAH patients. Given that the Chinese population represents a significant portion of the global population and the increasing incidence of stroke due to aging, optimizing patient care is vital. Given the current challenges in aSAH patient outcomes, initiating more prospective clinical trials is essential. Recent research has shown hydrogen’s therapeutic potential, aligning with EBI in aSAH, driving our exploration of hydrogen therapy’s mechanisms in post-aneurysm rupture damage.

**Ethics and dissemination:**

The protocol for the HOMA study was approved by the Ethics Committee of Beijing Tiantan Hospital, Capital Medical University (KY 2022–020-02). All results of the present study will be published in peer-reviewed journals and presented at relevant conferences.

**Trial registration:**

ClinicalTrials.gov NCT05282836. Registered on March 16, 2022.

**Supplementary Information:**

The online version contains supplementary material available at 10.1186/s13063-024-08231-5.

## Strengths and limitations of this study

This study endeavors to amalgamate hydrogen–oxygen gas inhalation with the concept of early brain injury subsequent to aneurysmal subarachnoid hemorrhage (aSAH), elucidating the prospective mechanisms underlying the efficacy of hydrogen–oxygen gas inhalation in the treatment of aSAH.Employing a legal hydrogen–oxygen generator equipped with a nebulizer for aSAH patients, this study not only addresses the safety concerns related to hydrogen preparation but also assures the secure clinical application of hydrogen therapy.The study’s primary objective is to explore the impact of hydrogen–oxygen gas inhalation therapy on the mitigation of delayed cerebral ischemia (DCI) and cerebral vasospasm (CVS), with a secondary aim of ascertaining whether this therapy can ameliorate the long-term prognosis of individuals afflicted by aSAH.It is imperative to note that this investigation is a single-center study. Consequently, should affirmative conclusions emerge, external validation will be imperative to bolster the reliability and generalizability of the findings.

## Background

Aneurysmal subarachnoid hemorrhage (aSAH) represents a prevalent neurosurgical emergency, characterized by a mortality rate spanning from 22 to 50%. Even among patients receiving optimal medical care, 40% of survivors contend with enduring physical disability or cognitive impairment, imposing a substantial healthcare burden on both families and the national medical infrastructure [1]. The concept of early brain injury (EBI), elucidating the pathophysiological changes unfolding within the brain during the initial 72-h post-aneurysm rupture, is now widely regarded as the primary driver of adverse patient outcomes [2, 3]. At this stage, marked by hemorrhagic release and accumulation, acute reactive hyperemia, and transient cerebral ischemia, the brain undergoes a cascade of responses, encompassing energy depletion, ionic perturbations, nitric oxide depletion, heightened endothelin-1 levels, inflammation, and oxidative stress [4–7]. Certain among these factors have been linked to grave complications, including delayed cerebral ischemia (DCI) and cerebral vasospasm (CVS), thereby elevating the peril of an unfavorable patient prognosis.[8].

While clinicians prioritize the prevention and management of DCI and CVS, it is imperative not to overlook other potential contributors to adverse patient outcomes. A recent review delved into the association between treating DCI or CVS and improving outcomes, with disheartening findings [9]. The occurrence of DCI and CVS may only encapsulate a fraction of the multifaceted mechanisms underpinning EBI-induced injury. Relying solely on the prevention and treatment of DCI or CVS presents two dilemmas: firstly, it may fall short in averting or reversing DCI or CVS, and secondly, even if DCI or CVS can be successfully managed, there may be no means to fully counterbalance the impact of other EBI mechanisms on patient prognosis. Thus, our hypothesis posits that an all-encompassing approach, targeting the spectrum of therapeutic objectives offered by EBI, is of paramount importance in averting severe complications and ameliorating patient outcomes.

Hydrogen, the most diminutive and copious element in our realm, possesses the attributes of rapid diffusion, non-toxicity, and benignity. In 2007, Ohsawa et al. pioneeringly postulated that inhaling a 2% hydrogen blend could selectively quell hydroxyl radicals and peroxynitrites, thereby significantly ameliorating the oxidative stress response induced by cerebral ischemia/reperfusion in a rat model of such ischemia–reperfusion [10]. Since that seminal discovery, hydrogen therapy has surged into the limelight, emerging as a focal point in disease treatment research [11–13]. As substantiated by prior investigations, hydrogen demonstrates its potency in mitigating oxidative stress-induced inflammatory responses, as evidenced by its capacity to down-regulate IL-1β, IL-6, chemokines, and TNF-α in various injury models [14–16]. Furthermore, hydrogen assumes roles in anti-apoptosis, anti-allergy, autophagy regulation, and enhanced energy metabolism [17, 18]. Beyond these chemical effects, its minuscule molecular weight enables unhindered penetration of brain cells via the blood–brain barrier, permeation of biofilms, and action upon therapeutic targets such as mitochondria. Considering these therapeutic facets, hydrogen manifests itself as ideally suited to combat the evolution of EBI following aSAH, offering distinctive advantages in cerebral protection subsequent to this condition. Preclinical evidence has demonstrated the efficacy of hydrogen and hydrogen–oxygen gas mixtures in improving behavioral outcomes and prognosis in murine models of experimental subarachnoid hemorrhage [19–22].

Nonetheless, the widespread clinical application of hydrogen has been hindered by challenges associated with its production and storage. Fortunately, China has recently achieved independent intellectual property rights and authorized hydrogen inhalation equipment, capable of generating a hydrogen–oxygen mixture via water electrolysis. Consequently, the time is ripe for an exploration of hydrogen’s role in aSAH treatment.

## Methods/design

Early *H*ydrogen–*O*xygen Gas *M*ixture Inhalation in Patients with *A*neurysmal Subarachnoid Hemorrhage: a randomized controlled trial (HOMA Trial) is a single-center, prospective, open-labeled, randomized controlled clinical trial in patients with acute aSAH at Beijing Tiantan Hospital. All patients are managed in alignment with the guidelines (such as maintaining euvolemia, avoiding hypo- and hypervolemia and repletion of volume and sodium losses, systolic blood pressure < 160 mmHg before aneurysm securement, and premorbidity blood pressure after aneurysm securement) [23]. Figure 1 shows the flow diagram of the study.

**Fig. 1 Fig1:**
[figure not shown]
Flow diagram of the study

### Patient population

HOMA is set to recruit 206 participants, evenly divided with 103 allocated to each treatment arm from China, to successfully execute the trial.

### Inclusion criteria

Age ≥ 18 years old;Emergency admission;Less than 48 h from the rupture to the admission and less than 24 h from the admission to surgical clipping or endovascular treatment;Written consent to participate in the study.

### Exclusion criteria

Previous SAH;History of neurosurgery due to any reasons;Physical disability or cognitive impairment due to any previous disease;Treatments including external ventricular drainage, lumbar puncture, angiography, intubation, and/or mechanical ventilation at other hospitals before presentation to our hospital;Pregnancy or breastfeeding;Any condition that imposes hazards to the patient due to treatment;Patients with foreseeable difficulties in attending follow-ups adequately;Patients with oxygen saturation < 88%;If oxygen saturation (SpO2) < 88% for patients in both groups, additional oxygen supplementation will be titrated to maintain SpO2 ≥ 88% by another oxygen concentrator. Patients will be allowed to withdraw from the study if SpO2 is still less than 88% when the total oxygen flow rate reached 7.0 L/ min.

### Randomization

Patients will undergo randomization performed by an intensive critical care (ICU) physician. Allocation will follow a 1:1 ratio through a stratified randomization approach. Allocation will be determined utilizing a minimization method of dynamic allocation, taking into consideration the preprocedural World Federation of Neurological Societies (WFNS) grade as a decisive factor.

### Treatment

Both hydrogen–oxygen mixture and oxygen are introduced via a nasal catheter.

Experimental arm: hydrogen–oxygen gas mixture inhalation therapy (8 h/day, 3 L/min, hydrogen concentration of 67%, oxygen concentration of 33%) daily for 1–7 days in the ICU ward.Control arm: oxygen gas inhalation therapy (8 h/day, 3 L/min, oxygen concentration of 33%) daily for 1–7 days in the ICU ward.d

The postoperative intervention of this study is administered by the assigned on-duty neurosurgeons in adherence to standardized operating protocols to enhance compliance.

### Primary outcomes

In-hospital DCI. DCI is diagnosed based on the following criteria: the emergence of new focal neurological deficits or a global neurological decline (defined as cerebral infarction identified on CT or MRI, after exclusion of procedure-related infarctions, and a decrease of ≥ 2 points on the Glasgow Coma Scale (GCS)) persisting for over 2 h [24]. This diagnosis is made after ruling out intracranial hemorrhage, hydrocephalus, seizures, metabolic imbalances, and infections, with or without radiographic evidence of cerebral vasospasm.In-hospital CVS. The diagnostic criteria for CVS encompass transcranial Doppler (TCD) sonography measurements (mean flow velocity exceeding 150 cm/s and/or Lindegaard index surpassing 3, and/or a TCD velocity increase exceeding 50 cm/s within 24 h), or cranial computed tomography (CT) angiography revealing vessel constriction exceeding 66%.

### Secondary outcomes and exploratory endpoints

The functional outcome will be evaluated by the modified Rankin scale (mRS) at discharge and 3 months after discharge via outpatient appointment.The cognitive outcome will be evaluated using the Montreal Cognitive Assessment (MoCA) at discharge and 3 months after discharge via outpatient appointment.Adverse events (AEs), including in-hospital pneumonia, intracranial infection, deep vein thrombosis (DVT), and stress ulcer bleeding.Mortality at discharge and 3 months after discharge.Radiographic score, including subarachnoid hemorrhage early brain edema (SEBES) score, modified Fisher scale (mFS) grade, Graeb score.Inflammation parameters, including white blood cell (WBC), neutrophil (NEUT), C-reactive protein (CRP), procalcitonin (PCT), IL-2, IL-6, IL-8, IL-10, TNF-α.Average blood flow velocities (BFVs) of anterior, posterior, and middle cerebral arteries.Levels of vascular endothelial growth factor (VEGF) and endothelin-1 (ET-1).

The detailed schedule of study assessments is shown in Table 1.

**Table 1 Tab1:** Schedule of enrollment, interventions, and assessments

Variables	Visit 1	Visit 2	Visit 3	Visit 4	Visit 5	Visit 6	Visit 7	Visit 8	Visit 8	Visit 9
	Admission within 72 h	Day 1 in ICU	Day 2 in ICU	Day 3 in ICU	Day 4 in ICU	Day 5 in ICU	Day 6 in ICU	Day 7 in ICU	Discharge	90 days
Participants										
Eligibility screen	×									
Informed consent	×									
Randomization		×								
Demographic data	×									
Interventions										
Surgical clipping or endovascular treatment	×									
Inhalation		×								
Assessments										
Modified Rankin scale	×								×	×
GCS	×	×	×	×	×	×	×	×	×	×
WFNS	×									
Hunt and Hess	×									
Modified Fisher	×									
Vital signs	×	×	×	×	×	×	×	×		
Inflammation parameters	×	×		×		×		×	×	×
VEGF	×	×		×		×		×	×	×
ET-1	×	×		×		×		×	×	×
Head CT	×	×						×	×	×
Head CTA + CTP	×								×	×
TCD				×			×			
MoCA									×	×
Adverse events		×	×	×	×	×	×	×	×	×
Detailed ICU therapy								×		
Inhalation time		×	×	×	×	×	×	×		
Inhalation volume		×	×	×	×	×	×	×		

*GCS* Glasgow Coma Scale, *WFNS* World Federation of Neurological Societies, *VEGF* vascular endothelial growth factor, *ET-1* endothelin-1, *TCD* transcranial Doppler

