### Patient and public involvement

Patients or the public have not participated in the design or execution of our research. Upon study completion, a manuscript will be prepared to present the trial findings. The final study results will be disseminated to all participants through the methods communicated at enrollment (mobile phone, WeChat, email, etc.).

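### The 3-month mRS is set at an outpatient visit with no other route named, so survivors too disabled to travel are plausibly the least likely to be scored

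*Protocol article*

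**What the plan says.** Under Secondary outcomes and exploratory endpoints, the protocol article assesses function by the "modified Rankin scale (mRS) at discharge and 3 months after discharge via outpatient appointment", and cognition by the "Montreal Cognitive Assessment (MoCA) at discharge and 3 months after discharge via outpatient appointment". Table 1 puts the mRS in the 90-day column together with head CT, CTA + CTP and blood markers, so that visit is in person. No telephone, carer, home or institutional assessment is mentioned. Death is a separate outcome, "Mortality at discharge and 3 months after discharge", with no mode attached.

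Strengths and limitations gives the trial a "secondary aim of ascertaining whether this therapy can ameliorate the long-term prognosis" of aSAH patients. The Background says that "40% of survivors contend with enduring physical disability or cognitive impairment". The Exclusion criteria remove "Patients with foreseeable difficulties in attending follow-ups adequately". The Statistical analysis section commits to intention to treat, reports adjusted odds ratios with values below 1 favouring hydrogen, and says that missing data are not to be expected.

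**The concern.** The ability to travel to one hospital is part of what the mRS grades. If a patient is scored only on coming to clinic, the worst-off survivors are the likeliest gaps, and missingness depends on the outcome itself. The exclusion does not remove the problem: it is judged at entry, whereas much of the relevant disability arises afterwards, from the bleed or its complications. The discharge mRS does not answer the 3-month question. Because the analysis section assumes complete data, the article offers nothing to absorb non-attendance.

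At stake is the secondary aim on long-term prognosis. It could in effect be answered for clinic attenders, although the plan promises intention to treat.

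**Working it through.** The plan gives no figure for 3-month attendance, attrition or mRS precision, so there is nothing of its own to reproduce on this point. Its only sample-size figure, 103 per arm, is for in-hospital DCI and CVS (23% v 45%, 90% power). A two-sided, continuity-corrected calculation gives 105, close to 103, and does not involve the mRS.

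**Inputs from the Background:** 40% of survivors with disability or cognitive impairment; mortality 22% to 50%. **Assumed, because the documents are silent:** 95% of unimpaired survivors attend, and 60% to 90% of impaired survivors attend.

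**1. Share of impaired among scored survivors.** With impaired share q and attendance a_d (impaired) and a_g (others), observed share = q·a_d / [q·a_d + (1 − q)·a_g]. At 60%: 0.40×0.60 / (0.40×0.60 + 0.60×0.95) = 0.24/0.81 = 29.6%, instead of 40%.

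| Impaired survivors unscored | Observed impaired share | All survivors unscored |
|---|---|---|
| 10% | 38.7% | 7% |
| 20% | 36.0% | 11% |
| 30% | 32.9% | 15% |
| 40% | 29.6% | 19% |

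**2. Deaths counted as poor outcome and fully known, 60%/95% attendance.**
- Mortality 22%: true poor share = 0.22 + 0.78×0.40 = 53.2%. Scored: (0.22 + 0.312×0.60) / (0.22 + 0.312×0.60 + 0.468×0.95) = 0.4072/0.8518 = 47.8%. The fall is 5.4 points.
- Mortality 50%: true 0.50 + 0.20 = 70.0%. Scored: (0.50 + 0.20×0.60) / (0.50 + 0.20×0.60 + 0.30×0.95) = 0.62/0.905 = 68.5%. The fall is 1.5 points.

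**3. Odds ratio among survivors, attendance depending on disability alone.** The observed odds in each arm are the true odds times a_d/a_g, which cancels. True shares of 30% v 40% give (0.30/0.70)/(0.40/0.60) = 0.643. At 60%/95% attendance the observed shares are 21.3% v 29.6% and the odds ratio is still 0.643. The risk difference shrinks from 10.0 to 8.3 points.

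**4. Two ways in which the odds ratio is biased.**
- *Attendance given disability differs by arm.* True null, 40% disabled in both arms. If 30% of disabled patients are unscored on hydrogen and 10% on control, the odds ratio is 0.70/0.90 = 0.78; with the arms reversed, 0.90/0.70 = 1.29.
- *Treatment moves patients between death and unscored disability.* Assume control 30% dead, 28% disabled, 42% good; hydrogen 20%, 38%, 42%. Poor outcome including death is 58% in both arms, so the true odds ratio is 1.00. Attendance is 60%/95% in both arms and deaths are known. Observed poor: hydrogen 0.20 + 0.38×0.60 = 0.428; control 0.30 + 0.28×0.60 = 0.468. Observed good is 0.42×0.95 = 0.399 in each. The odds ratio is 0.428/0.468 = 0.91, an apparent benefit with no difference in behaviour between arms.

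**The case against.** The strongest objection is that a condensed article need not describe what happens after a missed visit; a fallback may stand in the full protocol, which is not shown. In-person assessment also fits a visit that includes imaging, blood sampling and MoCA. This stands to a degree: a reader might infer that clinic attendance is the only permitted route and that non-attenders go unscored, but the article does not say so. What it does is state a mode, name no other, and tell the analyst not to expect missing data. That combination is a choice that can be improved, not merely omitted detail.

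Four other stronger readings fail.
- *Some 41 to 64 patients would be lost.* The arithmetic is 206×0.50×0.40 and 206×0.78×0.40, but the 40% includes ambulatory and purely cognitive cases, and the mortality range is a disease-wide background figure rather than one for patients meeting these entry criteria. It is at most a loose pool, not an expected loss.
- *The treatment comparison must be biased.* Step 3 shows that it need not be.
- *The trial already plans remote contact for outcomes.* The routes named under Patient and public involvement ("mobile phone, WeChat, email, etc") are for sending final results to participants.
- *The functional objective is about the most disabled.* The stated aim concerns aSAH patients generally, and deaths can be classified without a visit.

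Finally, telephone or carer ratings bring their own subjectivity in an open-label trial. That is true, and it is a cost of the fix.

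**Conclusion.** The concern holds in moderate form. Followed as written, the plan makes observation of the 3-month mRS plausibly dependent on the mRS itself, and the statistical section assumes the problem away. That disability hinders attendance is a reasonable inference; the documents contain no data on it, and every magnitude here rests on assumed attendance.

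Under those assumptions, disability among scored survivors is understated by about 1 to 10 points. At the least favourable attendance used (60%), the distortion once deaths are counted is about 5 points at 22% mortality and 1.5 points at 50%. Bias in the odds ratio is conditional: it needs attendance given disability to differ by arm (0.78 or 1.29 under a true null in the cases shown), or a shift between death and unscored disability (0.91 in the case shown). Only a secondary outcome is touched. DCI and CVS are in-hospital, and neither they nor the sample size are affected. The change is worth making because it is cheap, not because the trial's main result depends on it.

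**What to change.** In Secondary outcomes and exploratory endpoints, keep the clinic visit as the default for the 3-month mRS. For a patient who cannot attend, obtain the mRS by structured telephone or video interview with the patient or carer in the same visit window, with the same rule in both arms. Confirm vital status on that call, score deaths as mRS 6, and record the mode (clinic, remote, carer) and report it by arm.

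In Statistical analysis, replace the statement that missing data are not to be expected with a sensitivity analysis for any mRS still missing.

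The cost is a field on the case report form, a few calls by the trained clinicians, and an amendment: under the article's own Protocol amendment section, changes to outcomes or analyses go to the ethics committee and the registry. There will be some difference between clinic and remote ratings, and some rater subjectivity because treatment is open label; reporting mode by arm makes this visible. Since recruitment was expected to complete in March 2024, the new route helps only patients whose 3-month assessment is still ahead, but the sensitivity analysis can cover everyone.

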### Data collection and monitoring

The two clinicians will undergo standardized training for data collection. Their proficiency will be assessed prior to commencing data collection, and the inter-rater reliability between the two clinicians will be evaluated. Study data will be gathered using an electronic clinical report form in Castor EDC, a data management system compliant with good clinical practices. The Data Safety Monitoring Board (DSMB), comprising two independent clinicians and one methodologist, will scrutinize all AEs reported by enrolled patients from the time of consent up to 12 months after discharge. The DSMB will oversee the overall conduct of the trial and possesses the authority to modify or halt the study based on a safety data review. DSMB meetings will be convened annually via online video conferencing until the study’s completion. The Trial Steering Group is responsible for running the trial day-to-day and providing organizational support, consisting of a principal investigator, research assistant, recruitment, and assignment personnel. They will meet to review every 3 months and the ethics committee will perform an annual follow-up review.

